**Power**	**80%**	**90%**	**80%**	**90%**

Sample size	**52**	**69**	27	36

MCID: Minimum clinically important difference

The results for the OHS and the HHS at the 5% significance level, based on the best available estimates of MCID (5 and 7 score points respectively) are very similar. Both scores are intended to measure patient hip function, so it is not unexpected that the sample sizes obtained using these scores give very similar results. An adjustment to the significance level for multiple comparisons resulted in only a small increase (2-5 patients) in the required numbers.

In summary, this study will use two primary outcome measures the Oxford Hip Score and the Harris Hip Score. The aim will be to recruit 78 patients in each group as this will provide sufficient participants to obtain a power of 90% for both primary outcome measures. With an allowance for 10% drop-out, the total number of patients required will be **172**. If recruitment proves to be problematic during the course of the trial, then with the agreement of the trial steering committee the target will be lowered and the more usual 80% power level will be considered sufficient. For this scenario, the total number of patients required will be 120 (including 10% for drop-out).

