### Statistical analysis

The main analysis will investigate differences in the primary outcome measures, the Harris Hip Score and the patient-reported Oxford Hip Score, between the two treatment groups on an intention-to-treat basis. The differences between treatment groups will be assessed using an independent samples t-test at 12 months post-operatively at the 5% level. Test levels, for the two primary outcome measures will be adjusted using the methods of Holm-Bonferroni [19] to allow for the multiple comparisons. A linear regression analysis will also be used to quantify the effects of the treatment groups on each of the primary outcome measures, after adjusting for the effects of a range of other important, potentially confounding, factors (e.g. age, gender) recorded for each patient. Subsidiary analyses will report results of tests for secondary outcome measures and primary outcome measures at interim occasions. Interim analyses will be performed only where directed by the Data Monitoring Committee.

The second main statistical objective of the trial is to determine, and compare, the complication rate of RSA and THA at one year post-operatively. All complications will be recorded during the trial, and rates will be determined at 12 months post-operatively and compared between treatment groups using a chi-squared (at the 5% level).

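### The fallback total of 120 leaves about 54 patients per arm, which has no room for the multiplicity allowance, so power under the planned Holm-Bonferroni test is about 75–78% rather than 80%

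*Protocol article*

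**What the plan says.** All the sample size statements are in the Sample size section of the protocol article.

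- **Main target.** "The aim will be to recruit 78 patients in each group", which is said to give "sufficient participants to obtain a power of 90% for both primary outcome measures". Then: "With an allowance for 10% drop-out, the total number of patients required will be 172".
- **Multiplicity.** "An adjustment to the significance level for multiple comparisons resulted in only a small increase (2-5 patients) in the required numbers".
- **Fallback.** If recruitment is difficult, "then with the agreement of the trial steering committee the target will be lowered and the more usual 80% power level will be considered sufficient". The figure given is: "For this scenario, the total number of patients required will be 120 (including 10% for drop-out").

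Tables 1 and 2 give the numbers per arm at an unadjusted 5% level. For the Harris Hip Score (HHS; difference 7, SD 13) they are 55 for 80% power and 73 for 90%. For the Oxford Hip Score (OHS; difference 5, SD 9) they are 52 and 69.

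The Statistical analysis section fixes the test: "Test levels, for the two primary outcome measures will be adjusted using the methods of Holm-Bonferroni [19] to allow for the multiple comparisons". It makes no exception for a reduced target.

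**The concern.** The main target can be rebuilt from the larger tabulated requirement plus a multiplicity allowance plus drop-out. The fallback cannot be rebuilt in that way. Once drop-out is taken from 120, what remains is about the unadjusted HHS requirement, with nothing left for multiplicity.

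This matters because 120 is a figure to act on. The committee could release the trial from 172 – 120 = 52 patients on the understanding that each primary outcome keeps 80% power. It should know the power that it is accepting under the test that will be used.

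**Working it through.** **Inputs.** The tabulated numbers, differences and SDs, the allowance of 2–5 and the 10% drop-out come from the Sample size section; the Holm-Bonferroni test comes from the Statistical analysis section. Three assumptions are added:

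- Tests are two-sided with equal arms. This reproduces the tables.
- Both true differences equal the minimum clinically important difference.
- The correlation between HHS and OHS lies between 0.5 and 0.9. The article says only that it is strong.

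**1. Tables.** Noncentral-t sample sizes per arm:

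| Outcome | 80% power | 90% power |
|---|---|---|
| HHS, 7/13 | 55.1 (stated 55) | 73.5 (stated 73) |
| OHS, 5/9 | 51.8 (stated 52) | 69.1 (stated 69) |

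**2. Main target.** 73 + 5 = 78 per arm; 78 × 2 × 1.1 = 171.6, stated as 172. This match is why the allowance is read as per arm and as included.

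**3. Fallback.** Without a multiplicity allowance, 55 × 2 × 1.1 = 121, close to the stated 120. With the allowance:

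- +2: 57 × 2 × 1.1 = 125.4, so 126.
- +5: 60 × 2 × 1.1 = 132 (or 120/0.9 = 133.3, so 134 with equal arms).

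**4. Evaluable patients at 120.** 120 × 0.9 / 2 = 54 per arm (120 / 1.1 / 2 = 54.5 by the article's own inflation rule). HHS with the allowance needs 57–60.

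**5. Power.** Unadjusted figures are noncentral-t. Holm figures are simulated with at least 100,000 trials per setting: the smaller p-value is compared with 0.025 and, if that passes, the larger with 0.05. Ranges run over correlation 0.5 to 0.9.

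| Evaluable per arm | HHS, 5% | OHS, 5% | HHS, Holm | OHS, Holm |
|---|---|---|---|---|
| 54 | 79.2% | 81.6% | 75–76% | 76–78% |
| 60 | 83.3% | 85.5% | about 80% | 81–83% |
| 78 | 91.7% | 93.2% | about 90% | 90–92% |

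Under Holm, 78 per arm delivers the stated 90% and 60 per arm would deliver the stated 80%. So an allowance of 5 per arm is about the right size in both scenarios, and 120 with drop-out lacks it. An allowance of 2 (57 per arm) lies midway between 54 and 60, so HHS power there is about (75.5 + 80)/2 ≈ 78%.

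**The case against.** The best defence is that 120 is a fair rounding of 121, the unadjusted HHS figure with drop-out. At an unadjusted 5% level HHS power is 79.2% and OHS exceeds 80%. That is correct, and the gap between 54 and 55 carries no weight. By the same ×0.9 count, 172 leaves 77.4 rather than 78. The defence fails only because the planned test is not at an unadjusted 5%.

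It is also fair that the article does not show how 120 arose. It may be 2 × 55 with drop-out and no multiplicity allowance. It may be 2 × 60 with the allowance and no drop-out. It may come from OHS alone: 52 + 2 = 54 per arm, and 108/0.9 = 120 exactly. One therefore cannot say which allowance was dropped. On none of these routes does 120 hold both allowances for HHS, and the OHS-only route abandons the aim of powering both outcomes.

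A reader might infer a larger deficit. The documents do not support the following readings:

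- **Power of 70% (HHS) and 73% (OHS).** These are for each outcome tested at a fixed 2.5%, which is plain Bonferroni. So is a total of 150. The plan specifies Holm.
- **Power of 68–73%.** This is the chance of rejecting both nulls together. The article's wording is fairly read as power for each outcome; even 60 per arm gives only about 74–78% on the joint criterion. The chance of rejecting at least one at 54 per arm is about 78–86%.
- **HHS power of 67% unadjusted with SD 15.** The target of 78 rests on SD 13, so SD 15 would undercut the main target as well. It is no evidence of a slip in the fallback.

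**Conclusion.** The point holds in a limited form. With 10% loss, 120 gives the advertised 80% only without multiplicity adjustment. Under the planned Holm-Bonferroni test the shortfall is about 4–5 percentage points for HHS and 2–4 for OHS.

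The size depends on the assumed correlation, on both effects being at the minimum clinically important difference, and on a HHS SD of 13. Reading the allowance as +5 per arm is an inference from 73 + 5 = 78. The lack of room does not depend on that choice, since +2 already needs 57 per arm.

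Type I error control is not affected, and neither is the target of 172. The fallback applies only if recruitment fails and the committee agrees. This is a should-fix correction of a contingency figure, not a flaw in the main design.

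**What to change.** Restate the fallback sentence in the Sample size section in one of two ways:

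- **Keep 120.** State that, after 10% loss, about 54 patients per arm give about 75% power for HHS and 77% for OHS under Holm-Bonferroni, with the assumed correlation.
- **Keep 80%.** Repeat the main target's steps: (55 + 5) × 2 × 1.1 = 132, or 134 if drop-out is applied by dividing by 0.9. With an allowance of only 2 the total is 126, but HHS power is then about 78%, so 132 is the better-supported figure.

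In either case, say whether the 2–5 patients are per arm and included, and give the steering committee the corrected figure before any reduction. The cost is one reworded sentence. If the 80% route is chosen, the contingency total rises by 12 patients. Nothing else in the plan changes.

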### Randomisation

A randomisation sequence has been independently generated on a computer. The sequence is stratified by supervising consultant orthopaedic surgeon. The randomisation sequence will be held by the Clinical Trials Unit of the University of Warwick. After patients have consented to take part in the trial, pre-operation outcome scores will be collected. Thereafter, the randomisation officer will be alerted by telephone of a new enrolment. The randomisation officer will provide the surgeons secretary with the treatment allocation for the patient which will then be entered onto the hospital system.

### Blinding

Before this trial was designed, patients undergoing resurfacing arthroplasty of the hip in our department were given a different pre-operative information sheet from those having a total hip arthroplasty; this reflected the existing evidence regarding the different risk/benefit profile of the two procedures. Therefore, we do not consider it ethical to blind the patients to their treatment allocation within the trial. The patients will be informed, by letter, of their treatment allocation in the week after they have given their consent. However, we will collect pre-operative information about the patients' preference for one or other treatment.

The consultants will, of course, not be blind to the treatment but will take no part in the post-operative assessment of the patients.

The research associate who performs the pre- and post- treatment outcome measurements will be blind to treatment allocation throughout the entire study. Patients will be asked not to discuss their allocated treatment with the research associate.

### Statistical analysis

The main analysis will investigate differences in the primary outcome measures, the Harris Hip Score and the patient-reported Oxford Hip Score, between the two treatment groups on an intention-to-treat basis. The differences between treatment groups will be assessed using an independent samples t-test at 12 months post-operatively at the 5% level. Test levels, for the two primary outcome measures will be adjusted using the methods of Holm-Bonferroni [19] to allow for the multiple comparisons. A linear regression analysis will also be used to quantify the effects of the treatment groups on each of the primary outcome measures, after adjusting for the effects of a range of other important, potentially confounding, factors (e.g. age, gender) recorded for each patient. Subsidiary analyses will report results of tests for secondary outcome measures and primary outcome measures at interim occasions. Interim analyses will be performed only where directed by the Data Monitoring Committee.

The second main statistical objective of the trial is to determine, and compare, the complication rate of RSA and THA at one year post-operatively. All complications will be recorded during the trial, and rates will be determined at 12 months post-operatively and compared between treatment groups using a chi-squared (at the 5% level).

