### Sample size

Previous work has shown the Oxford Hip Score (OHS) and the Harris Hip Score (HHS) to be reliable measures of hip function after surgery, as measured by Cronbach's alpha statistic for internal consistency [10,14]. Correlation analysis has indicated that both measures are reproducible, i.e. their test-retest reliability is good, and previous studies [15] have shown them to be strongly correlated, indicating that both scoring systems are measuring the same latent characteristic (hip function). However, the self-administered OHS has achieved much higher follow-up rates than the more widely used HHS [15]. Therefore, in order to provide the best assessment of patient experience of hip function after surgery and also to allow dissemination of the results of this trial to as wide a potential audience as possible in resulting publications, we prudently choose to use both the OHS and the HHS as primary outcome measures.

Harris Hip Score. There is less available specific information on previously observed variability for the HHS, than for the OHS. Assuming Normally distributed scores, the required numbers of patients in each arm of the trial are shown in Table 1, based on an independent samples t-test (at the 5% level) for assumed standard deviations (SD) of 13 and 15 [15] and minimum clinically important differences (MCIDs) of 7 and 10 [16](PS, power and sample size software, available at http://biostat.mc.vanderbilt.edu/wiki/Main/PowerSampleSize

**Table 1 T1:** Patient number required for MCID in Harris Hip Score at different power levels.

	MCID = 7		MCID = 10	
**Power**	**80%**	**90%**	**80%**	**90%**

SD				

13	**55**	**73**	28	37

15	73	97	36	48

MCID: Minimum clinically important difference

The minimum clinically important differences used for this sample size calculation give effect sizes of around 0.6; a medium to large effect size using the conventional descriptions of these terms [17]. More reliable data for determination of the MCID is available for the OHS.

Oxford Hip Score. The best estimate for the standard deviation for the OHS is 9 and the MCID is between 5 and 7 points on the OHS scale, calculated from a previous comprehensively reported study [18]. Using these estimates the required numbers of patients in each arm of the study, for a two-sample t-test (at the 5% level) are shown in Table 2.

**Table 2 T2:** Patient number required for minimum MCID in Oxford Hip Score at different power levels.

	MCID = 5		MCID = 7	

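### The deciding analysis is an unadjusted t-test, although the pre-operative score and the stratifying surgeon are on record: an avoidable loss of precision

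*Protocol article*

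**What the plan says.** The Statistical analysis section of the protocol article makes the between-group comparison of the Harris Hip Score (HHS) and Oxford Hip Score (OHS) the main analysis: "The differences between treatment groups will be assessed using an independent samples t-test at 12 months post-operatively at the 5% level". It controls multiplicity across the two scores: "Test levels, for the two primary outcome measures will be adjusted using the methods of Holm-Bonferroni". A linear regression is then planned in addition, adjusting for a range of "potentially confounding, factors (e.g. age, gender) recorded for each patient".

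The Sample size section rests on the same unadjusted test. For the OHS the required numbers "for a two-sample t-test (at the 5% level) are shown in Table 2", and the HHS table is built in the same way.

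The Randomisation section shows what is known before allocation. On the design, "The sequence is stratified by supervising consultant orthopaedic surgeon". On the data, "After patients have consented to take part in the trial, pre-operation outcome scores will be collected", and only after that is the randomisation officer contacted. The section on post-randomisation withdrawals adds that surgical approach and fixation are left to the consultant.

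**The concern.** Two variables that could explain part of the variation in the 12-month scores are available for every patient before allocation: the same score measured pre-operatively, and the consultant who defines the randomisation stratum. The deciding test uses neither, so whatever variation they explain stays in the error term. Any chance imbalance in pre-operative function also stays in the primary estimate.

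The article itself treats pre-operative function as important. Its Background faults an earlier non-randomised comparison partly because the groups differed on pre-operative functional scores.

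At stake are the width of the confidence interval and some power. This matters most if the trial falls back to its reduced recruitment target, or if the HHS varies more than the planning value.

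**Working it through.** **Inputs from the Sample size section.** HHS: difference 7, SD 13 (alternative SD 15). OHS: difference 5, SD 9 ("The best estimate for the standard deviation for the OHS is 9 and the MCID is between 5 and 7 points on the OHS scale"). Planned 78 per group before the drop-out allowance. Fallback 120 in total including 10% drop-out. Sidedness is not stated; a two-sided 5% level reproduces the tables.

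**Inputs not in the documents (assumptions).** The correlation r between pre-operative and 12-month score, taken as 0.2 to 0.5. The surgeon intraclass correlation (ICC), taken as 0.02 to 0.10. The correlation between the two primary outcomes, called strong in the article but given no value, taken as 0 to 0.9.

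**Step 1: reproduce the plan's figures.** n per arm = 2(1.960 + 1.282)² (SD/difference)² at 90% power.
- HHS: 2 × 10.51 × (13/7)² = 72.5, so 73, as in Table 1.
- OHS: 2 × 10.51 × (9/5)² = 68.1, so 69, as in Table 2.

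**Step 2: power of the planned t-test at 78 per arm.** The noncentrality is difference / (SD√(2/78)): 3.36 for HHS and 3.47 for OHS, on 154 degrees of freedom.
- At 0.05: HHS 0.916, OHS 0.932.
- At 0.025 (first Holm step): HHS 0.863, OHS 0.885.

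Under Holm, HHS is rejected if it passes 0.025, or if it passes 0.05 while OHS passes 0.025. With independent outcomes:

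0.863 + (0.916 − 0.863) × 0.885 = 0.910.

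Simulation with outcome correlations from 0 to 0.9 gives 0.912 down to 0.895 for HHS and 0.927 down to 0.904 for OHS. The stated 90% is essentially met.

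**Step 3: add the pre-operative score.** Residual variance is multiplied by (1 − r²), so SD becomes SD√(1 − r²). The table repeats Step 2, taking the outcomes as independent in the Holm columns and using unrounded powers.

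| r | 1 − r² | HHS at 0.05 | HHS at 0.025 | OHS at 0.025 | HHS, Holm | OHS, Holm |
|---|---|---|---|---|---|---|
| 0 | 1.00 | 0.916 | 0.863 | 0.885 | 0.910 | 0.925 |
| 0.2 | 0.96 | 0.927 | 0.877 | 0.898 | 0.922 | 0.935 |
| 0.3 | 0.91 | 0.939 | 0.895 | 0.914 | 0.935 | 0.947 |
| 0.4 | 0.84 | 0.954 | 0.919 | 0.935 | 0.952 | 0.962 |
| 0.5 | 0.75 | 0.971 | 0.946 | 0.958 | 0.970 | 0.977 |

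The HHS gain is therefore about 1, 2.5, 4 and 6 points. Correlation between the outcomes lowers the levels a little. Allowing for it, HHS power is about 0.90-0.91 unadjusted and about 0.91-0.92, 0.93, 0.95 and 0.97 adjusted. In patients, the precision of 156 evaluable under the t-test would need 156 × (1 − r²) = 150, 142, 131 or 117 under the adjusted model.

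**Step 4: where the plan has less slack (HHS, level 0.05).**
- Fallback: 120 × 0.9 / 2 = 54 per arm. Power 0.792 unadjusted, 0.857 at r = 0.4, 0.893 at r = 0.5.
- SD 15 at 78 per arm: 0.825 unadjusted, 0.885 at r = 0.4, 0.917 at r = 0.5.

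**Step 5: surgeon alone.** If allocation is balanced within surgeon, the adjusted residual variance is multiplied by (1 − ICC). At ICC 0.02, 0.05 and 0.10 the unstratified t-test's actual level is about 0.048, 0.044 and 0.039. Adjusting for surgeon moves HHS power (level 0.05, 78 per arm) from 0.919 to 0.922, 0.923 to 0.929, and 0.928 to 0.941.

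**The case against.** The strongest reply is that nothing here is wrong. A t-test after randomisation is valid and unbiased, it matches the test used for the sample size, and the trial reaches its stated power with it. That stands, and it limits the point to efficiency.

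It can also be said that the planned regression already covers this. Its covariates are given only as examples, the pre-operative score and surgeon are recorded, and a condensed article may leave the full list to the analysis plan. That also stands as far as the regression goes: its not naming these variables is no fault. But the regression is additional, and the article positively names the t-test as the main analysis, so a fuller covariate list would not change which result decides the trial.

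Three stronger readings are tempting, and the documents support none of them:
- **That the trial is underpowered at about 86% (HHS) and 88% (OHS).** Those are powers at the 0.025 first step alone. The plan uses Holm, and with both planned effects present each score's power is about 0.90 or more.
- **That the t-test's standard error is too large for the design.** This needs balance within surgeon. The article states stratification but no blocking, and even with balance the test is only mildly conservative at the ICCs considered.
- **That two analyses compete without a ranking.** They may differ numerically, but the article ranks the t-test as main.

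**Conclusion.** The point holds as an avoidable loss of precision in the deciding analysis, not as an error of validity or sample size. At the planned 78 per arm under Holm, the gain forgone on HHS runs from about 1 point of power at r = 0.2 to about 6 points at r = 0.5, and slightly less on OHS. In the 120-patient fallback it is about 6.5 to 10 points for r of 0.4 to 0.5 (0.857 − 0.792 and 0.893 − 0.792). With an HHS SD of 15 it is about 6 to 9 points (0.885 − 0.825 and 0.917 − 0.825).

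Nearly all of this comes from the pre-operative score; surgeon contributes about 1 point at ICC up to 0.10. The size depends on r and the ICC, which the documents do not give. If r were 0.2 or less, the practical gain at full recruitment would be small.

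**What to change.** Restate the main analysis of each primary score as a linear model of the 12-month score on treatment, the same score's pre-operative value and consultant surgeon. The number of surgeons is not stated; if there are many, use a random effect or pool those with few patients, and specify which in advance. Apply Holm to the two treatment p-values from these models. Keep the independent samples t-tests as a supporting analysis.

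The cost is a change of wording in the Statistical analysis section, made before outcome data are seen. Both covariates are already recorded, so no new data are needed, and the sample size can stay as it is.

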### Economic analysis

The economic evaluation will estimate the incremental cost effectiveness of RSA compared to THA from the perspective of the UK NHS. A within trial (12 month) analysis will be conducted, with lifetime results extrapolated from trial data, registry data, and the literature using a patient level simulation model. These analyses will have common features: both will use a quality-adjusted life-year (QALY) outcome measure based on EQ-5D data and the 10 year MVH TTO tariff [20]; both will use a payer (NHS and Social Services) perspective for the main case analysis; costs will be obtained from resource using national databases (NHS Reference Costs, the BNF, and PSSRU Costs of Health and Social Care) and local data sources (UHCW finance department).

The within trial analysis will consider cost-effectiveness within the first 12 months of treatment. This analysis will be based on quality of life data collected at discharge (baseline) and at 3, 6, and 12 months post operatively, with QALYs obtained by calculating the area under the curve. Resource usage will be estimated from trial forms plus patient questionnaires detailing other NHS contacts and personal expenditures within the trial period, with costs assessed as above.

As hip replacement and failure of hip replacements may have an impact upon mortality as well as morbidity, it will be necessary to adopt a lifetime time horizon to estimate the full incremental value of RSA compared to THA. Therefore we will construct a patient-level decision analytic cost effectiveness model to estimate the expected incremental cost per life year gained for RSA compared to THA. Whilst the trial dataset will be used to provide parameters for several states, the main data sources for the extrapolation will come from existing literature and registries as the model horizon greatly exceeds the trial length. The model will comprise states specific to both RSA and THA (surgery, recovery, success and failure), with adjustments for THA revision surgeries (as feasible). Quality of life figures will be obtained from a combination of trial data and literature/registries. Mortality will be represented using age/gender specific rates, with additional mortality assigned in surgical, recovery and failure states (as feasible). Failure rates for devices will be based on survival analysis, with the type and complexity of relationships determined by Bayesian decision criteria. Costs will be obtained from the within-trial analysis by status and used to inform state-specific costs, with existing literature and expert judgement used where necessary. The model will use a standard discount rate of 3.5 and parameter uncertainty will be addressed through probabilistic sensitivity analysis, with any inflation-adjustments based on the HCHS Pay and Prices Index. Wherever possible, the results of all analyses will be presented in a simple, easy to follow manner using standard techniques within economic evaluation. Outputs of each analysis will be presented as Cost Effectiveness Acceptability Frontiers and Expected Net Benefit figures assuming that the cost-effectiveness threshold lies at £30,000 per QALY.

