**Methods/design:**

All patients medically fit for surgery and deemed suitable for a resurfacing arthroplasty are eligible to take part in this study. A randomisation sequence will be produced and administered independently. After consenting, all patients will be clinically reviewed and hip function, quality of life and physical activity level will be assessed through questionnaires. The allocated surgery will then be performed with the preferred technique of the surgeon. Six weeks post-operation hip function will be assessed and complications recorded. Three, six and 12 months post-operation hip function, quality of life and physical activity level will be assessed. Additional information about patients' out-of-pocket expenses will also be collected.

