#### Follow-up

Patients will continue in routine clinical follow-up, as per their surgeon's practice. For this trial, the primary outcome point will be at one year, with other planned assessments at six weeks, 3 months and six months after operation. At all these occasions patients will come to the clinic to be reviewed by the research associate and if necessary a doctor.

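### The within-trial QALY curve starts from a discharge EQ-5D labelled baseline, but the described schedule has no such assessment, and a value taken after randomisation and surgery is not a baseline

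*Protocol article*

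**What the plan says.** For the within-trial evaluation, the Economic analysis section names these inputs: "quality of life data collected at discharge (baseline) and at 3, 6, and 12 months post operatively". The method that turns them into QALYs is given as follows: "with QALYs obtained by calculating the area under the curve". The section also fixes the horizon: "The within trial analysis will consider cost-effectiveness within the first 12 months of treatment".

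The assessment schedule is described in three other places.

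- **Abstract, Methods/design**, before surgery: "After consenting, all patients will be clinically reviewed and hip function, quality of life and physical activity level will be assessed through questionnaires". After surgery: "Six weeks post-operation hip function will be assessed and complications recorded", and then "Three, six and 12 months post-operation hip function, quality of life and physical activity level will be assessed".
- **Follow-up** sets the primary time point at one year, "with other planned assessments at six weeks, 3 months and six months after operation".
- **Randomisation**: "After patients have consented to take part in the trial, pre-operation outcome scores will be collected". Only then is the randomisation officer contacted for the allocation.

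Discharge is mentioned in two further places, neither of which involves the EQ-5D. Rehabilitation keeps a photocopy of a discharge letter. Outcome measures refers to costs arising after discharge, collected at 3, 6 and 12 months.

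**The concern.** The QALY calculation names a first measurement that the described schedule does not contain. It also gives the word baseline to a value taken after allocation and after the operation. Patients are not blinded and learn their allocation by letter within a week of consent (Blinding section). A discharge EQ-5D may therefore already reflect the procedure, in-hospital complications and knowledge of treatment. The value that is free of these influences, the pre-operative one, is missing from the list of QALY inputs.

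Cost-effectiveness is one of the three main objectives (Study objectives), and trial quality-of-life data also feed the lifetime model. An analyst following the text could find no value with which to start the curve, or could take a post-treatment value as the baseline.

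**Working it through.** **1. The two accounts side by side**

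| Time | Quality of life in the schedule | Input to within-trial QALYs |
|---|---|---|
| Before operation, before allocation | Yes | Not listed |
| Discharge | Not listed | Yes, called baseline |
| 6 weeks | Not named (hip function and complications only) | No |
| 3 months | Yes | Yes |
| 6 months | Yes | Yes |
| 12 months | Yes | Yes |

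The last three QALY points match the schedule. The first does not. Leaving out six weeks is consistent in both accounts.

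**2. Weight of the first point.** The protocol states no QALY figure, so there is none to reproduce. With times of 0, 0.25, 0.5 and 1 year, the trapezoid weights are:

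- first point: (0.25 − 0)/2 = 0.125
- 3 months: (0.5 − 0)/2 = 0.25
- 6 months: (1 − 0.25)/2 = 0.375
- 12 months: (1 − 0.5)/2 = 0.25

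They sum to 1, so the first point carries 12.5%.

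**3. Effect of choosing one first point over the other.** Let D_dis and D_pre be the between-arm differences in mean EQ-5D at discharge and before operation. Replacing one by the other at time zero moves the incremental QALY by 0.125 × (D_dis − D_pre). A change from pre-operation to discharge that is equal in both arms cancels. The protocol gives no EQ-5D values, so the gap is assumed; the threshold of £30,000 per QALY is the protocol's own.

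| Assumed D_dis − D_pre | QALY shift (× 0.125) | Value (× £30,000) |
|---|---|---|
| 0.02 | 0.0025 | £75 |
| 0.10 | 0.0125 | £375 |
| 0.30 | 0.0375 | £1,125 |

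**4. Why the pre-operative value is also wanted as a covariate.** This is a separate quantity and does not measure the cost of using discharge. Assume an EQ-5D SD of 0.3, with the planned 78 per arm. One standard error of chance pre-operative imbalance is 0.3 × √(2/78) = 0.048. If later values correlate with the pre-operative value at ρ (equal SDs assumed), that imbalance moves an unadjusted QALY difference, on a curve starting before operation, by 0.048 × (0.125 + 0.875ρ):

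- ρ = 0.3: 0.048 × 0.3875 = 0.019 QALY, about £560
- ρ = 0.5: 0.048 × 0.5625 = 0.027 QALY, about £810

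Regression on the pre-operative EQ-5D addresses this.

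**5. If a discharge value exists and is added as an extra point.** At time t after surgery (in years), the pre-operative point takes weight t/2, discharge (0.25 − 0)/2 = 0.125, and 3 months (0.5 − t)/2. For a short stay this curve is close to the one that the Economic analysis section describes. What changes is which value is called baseline and used for adjustment.

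**The case against.** The strongest reply is that this is a one-line inconsistency in a condensed article. Discharge may be a slip, with baseline as the intended word; the pre-operative EQ-5D would then be the first point after all. Alternatively, an inpatient form completed at discharge may exist in the full protocol. The Follow-up section lists clinic visits and would not mention such a form, and the Economic analysis section itself speaks of data collected at discharge. So a reader might infer that the first point will not exist, but the article cannot establish that. What stands is that the two descriptions disagree and that one of them must change.

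A second reply is that a post-operative value is not wrong in an area under the curve. The horizon is the first 12 months of treatment, and an early difference between arms is a real QALY effect. That is correct. Step 5 shows that such a point would be legitimate if it were scheduled. The fault is confined to the baseline label and the missing schedule entry.

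Three further inferences are tempting and unsupported:

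- That baseline imbalance could not be corrected. Pre-operative scores are collected before allocation, so it could.
- That baseline adjustment will remove early treatment effects. The Economic analysis section states no covariate adjustment for QALYs; the harm would arise only if the discharge value were used that way.
- That the pre-operative EQ-5D has no use anywhere. It is unlisted for the within-trial QALYs, but the covariates in Statistical analysis are left open and the lifetime model draws on unspecified trial data.

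**Conclusion.** The point holds as an internal contradiction with a mislabelled baseline. The first QALY time point conflicts with the described schedule, and a value taken after randomisation and surgery is not a baseline. That point carries 12.5% of the weight in the 12-month area, given trapezoids and a first value placed at time zero. The monetary figures are illustrations that rest on assumed EQ-5D differences, SD and correlations; none is an estimate of bias in this trial.

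Severity is moderate. A stated main objective is affected, whereas the primary outcomes, their tests, the complication comparison and the sample size are not. The lifetime model relies mainly on literature and registries, which limits how far the problem carries forward. The absence of an EQ-5D at six weeks is not part of this finding.

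**What to change.** Reconcile the Economic analysis section with the Abstract, Follow-up and Randomisation sections:

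1. Name the pre-operative, pre-randomisation EQ-5D as the baseline.
2. Compute the area under the curve from that value through 3, 6 and 12 months.
3. Estimate the QALY difference by regression on treatment, with pre-operative EQ-5D and surgeon (the stratification factor) as covariates.
4. If a discharge EQ-5D is in fact collected, add it to the schedule and use it only as an additional post-operative point, never as the baseline covariate.

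The first three steps cost a sentence or two of text and use data already collected. The fourth adds one schedule entry, and only if the measurement is being made. No change to the sample size is needed.
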